#### 2.8.2. Dependent Variables

BMI at 2 years of life.Percentage of fat mass at 2 years of life.

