The project’s global hypothesis is that an intervention in the first 1000 days of life on the early programming factors related to childhood obesity will achieve more adequate early programming and will decrease the prevalence of childhood obesity. The risk of developing obesity in childhood will be lower when the number of factors accumulated in the individual in this critical first phase is decreased. This improvement in early metabolic programming will be reflected in a lower percent of body fat mass at 2 years of age, compared to the control group.

The aim of the project is to evaluate the effectiveness of a combined multifactorial educational and care intervention for preventing obesity and overweight in childhood, based on the concept of early programming, and developed during pregnancy and the first 2 years of life (the first 1000 days) by a multidisciplinary group in primary care. The specific objectives are:

To analyse the body fat mass at 2 years of age in a control group of children who reach this age between November 2017 and June 2019, belonging to two pediatric quotas of the Basic Health Zone (BHZ) of Puerto Real.

To analyse the body fat mass at 2 years of age in the intervention group of children, whose pregnancies begin between January and December 2018, belonging to four pediatric quotas of the BHZ of Puerto Real. 

To compare the body fat mass at 2 years of age between the control and intervention groups.

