### 2.4. Recruitment

A single midwife will take charge of maternal education in the CMU Puerto Real, which includes the Ribera del Muelle Health Centre where there are three paediatricians, and the Rio San Pedro Health Centre where there is one. Therefore, all pregnant women will receive exactly the same information about the intervention. After birth, the parents will decide in which of the six paediatricians of the BHZ of Puerto Real they will register their children, and we cannot interfere in that decision.

The study population of the control group will be constituted by two-year-old children of two quotas of the Basic Health Zone of Puerto Real. The paediatricians have employment stability for at least the expected duration of the study and have agreed to participate. The inclusion in the study and the data collection will be carried out in the health controls at 2 years of age at the same time as the intervention in pregnant women begins, so that neither mothers during pregnancy nor infants after delivery will have been influenced by the intervention. Once the intervention ends, their results will be analyzed from the data obtained from the mother–child pairs.

Following the above criteria, all newborns assigned to the four pediatricians of the unit that meet the inclusion criteria will be included in the intervention group. Two paediatricians from the same unit will also participate in the data collection for the control group. Including a greater number of pediatricians is necessary to obtain the calculated sample of the intervention group, due to the decrease in the birth rate observed in recent years. Inclusion in the study will be done at the first pediatric visit of the newborn.

The inclusion criteria are: two-year-old infants whose pregnancy begins in the 14 months following the start of the intervention, and whose mothers have made the complete follow-up of their pregnancy in the Care Process of Pregnancy Childbirth and Puerperium and begun the monitoring of child health controls of the Andalusian Children and Adolescents Health Program in our unit. The exclusion criteria are: infants whose parents do not authorize their participation in the study in writing.

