### 2.6. Retention

The control group does not need incentives to continue in the study since, once their participation is accepted, the data of the mother–child pairs are taken and do not require any other action. The participants of the intervention group, once their participation in the first month’s visit has been accepted, only have to go to the usual health checks until 2 years. At these ages, parents are very receptive to participate in all initiatives that can improve the health of their children, especially if they are developed by the usual professionals. We consider that they will remain in the study without difficulty.

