### 2.9. Data Collection 

The data for the control group will be collected through a data collection sheet, specifically designed for the study, from three sources: (1)Direct questions to the parents at the one-year and two-year visits, performed by paediatricians.(2)The weight, height and BMI records of the Diraya program, both for pregnant women and children.(3)Mothers and children’s medical records from the Diraya program. The form will be subsequently computerized.

The data for the intervention group will be collected in the same way, but also at the newborn and six-month visits, developed by paediatricians.

The midwives in the usual CPPCP controls will collect the gestational and delivery variables. Nurses and paediatricians in the usual controls of the A-CAHP will collect the somatometric variables of newborns up to 2 years.

After childbirth, during the puerperal visit, the midwife will register the birth data in the Diraya program as a hospital visit. If the mother does not attend the puerperal visit, it will be the paediatricians at the newborn visit who will collect the data from birth.

The weight and height of pregnant women will be measured with an ADE (GmbH & Co, Hamburg, Germany) scale, model M304641-01, with a reading range from 2 to 250 kg and a precision of 100 g, with an ADE stadiometer coupled to the scale, model MZ10023-1, with a reading range of 60–210 cm and a precision of 0.1 cm.

Weights will be measured in the first and second year of age with the child naked on a Soehnle baby scale, reading in a range of 0–20 kg with a 10 g precision. The length will be measured with the infant in supine position with a rigid Añó-Sayol stadiometer, with a reading range of 25 to 90 cm and an accuracy of 0.5 cm. The tables of weight, length and BMI values of the WHO will be used.

The skin folds will be measured with a Holtain Skinfold Caliper plicometer with an amplitude of 0–46 mm, 0.2 mm graduation and a constant pressure of 10 g/mm^2^. They will be measured in the left side of the body, in triplicate and by a single observer for each pediatric quote, according to universally recommended techniques [62,63].

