### 2.10. Data Analysis

For the statistical analysis of these data, the statistical program SPSS Version 22 software (IBM Corp, Armonk, NY, USA, 2015) will be used:

Descriptive analysis. The means and standard deviations for the quantitative variables and the absolute and relative frequencies for the qualitative ones will be determined.

Bivariate analysis. The Kolgomorov–Smirnov test will be used to determine if the quantitative variables are parametric; when the sample is less than 50, the Shapiro–Wilk test will be used. For the comparison of the dependent variables with qualitative independent ones, we will use the Student’s *t*-test and ANOVA for independent means as a test of statistical significance, and the Mann–Whitney U and the Kruskall–Wallis tests for the nonparametric ones. For independent quantitative variables, the Pearson and Spearman coefficients will be used.

Multivariate analysis. The analysis of the degree dependent variables with the independent variables will be carried out using the generalized linear model. For the linear regression, we will use the Gaussian family and as a function of the identity bond and for the binary logistic regression, the binomial family and the logit link function.

To detect differences, a significance level *p* < 0.05 will be used and the 95% confidence intervals will be calculated.

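### Age at the 2-year measurement is neither fixed by a visit window nor listed as a covariate, so any difference in mean visit age between the two cohorts would stay in the group contrast, most clearly for percent fat mass.

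*Protocol article*

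**What the plan says.** All references are to the protocol article.

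- **Outcomes (2.8.2):** "BMI at 2 years of life.Percentage of fat mass at 2 years of life". Neither is described as a z-score, a centile or an age-adjusted value.
- **Covariates (2.8.1):** a detailed list that includes newborn sex. Age or date at the 2-year measurement is not on it.
- **Reference tables (2.9):** "The tables of weight, length and BMI values of the WHO will be used". The text does not say how the tables enter the BMI outcome, and they do not extend to percent fat mass.
- **Analysis (2.10):** for qualitative factors, "we will use the Student’s *t*-test and ANOVA for independent means as a test of statistical significance", with rank tests as the alternative. Then "The analysis of the degree dependent variables with the independent variables will be carried out using the generalized linear model".
- **Timing of measurement:** for controls (2.4), enrolment and measurement "will be carried out in the health controls at 2 years of age at the same time as the intervention in pregnant women begins". Intervention children (2.6) "only have to go to the usual health checks until 2 years". Neither section gives a window in days or months.
- **Calendar periods (Introduction, specific objectives):** a "control group of children who reach this age between November 2017 and June 2019", against intervention children whose pregnancies begin during 2018. Section 2.7 extends the first pregnancy visits to February 2019.

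**The concern.** BMI and body fat change with age in early childhood, so what is recorded at a 2-year visit depends partly on when the child attends. In a randomised trial, visit age would balance on average. Here the control group is historical and nothing in the design balances it.

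The two groups also reach the measurement differently. Controls are enrolled and measured at the 2-year visit itself, in two paediatric quotas. Intervention children are enrolled at the first newborn visit and followed through scheduled checks, in four quotas. These are reasons not to take equal mean ages for granted. They do not show that the ages differ.

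At stake is the main comparison. A difference in mean visit age would appear as part of the intervention effect, in either direction, and age spread within groups would add noise that a covariate could remove. The plan already allows for elapsed time in one place: early infant weight gain is expressed per day (2.8.1). The outcomes get no such allowance.

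**Working it through.** The plan gives no figure for age at the visit, for the change of either outcome with age, or for an outcome SD, so there is no figure of its own to reproduce on this point.

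**1. Calendar separation.** Controls turn 2 from November 2017 to June 2019; the midpoint is about the end of August 2018. Pregnancies starting January to December 2018, plus an assumed 266-280 days of gestation and 2 years, give second birthdays from about late September or early October 2020 to about the same point in 2021; the midpoint is about late March or early April 2021. The midpoints are about 2.6 years apart, and the nearest edges about 15 months. With the February 2019 limit in 2.7, the last birthdays move to about late November or early December 2021.

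**2. BMI.**

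From 2.5: 100 control and 150 intervention children, 15% loss (leaving 85 and 127.5), alpha 0.05, taken as two-sided. Assumed: SD 1.3 kg/m2; BMI changing by 0.02-0.08 kg/m2 per month near age 2; a gap in mean visit age of 1 or 2 months.

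- SE = 1.3 × sqrt(1/100 + 1/150) = 0.168. After loss: 1.3 × sqrt(1/85 + 1/127.5) = 0.182.
- Spurious shift = slope × gap. For 2 months: 0.04 to 0.16 kg/m2.
- Type I error = Φ(shift/SE − 1.96) + Φ(−shift/SE − 1.96).

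| Gap | Slope per month | Shift | Shift/SE (100 v 150) | Type I, 100 v 150 | Type I, 85 v 127.5 |
|---|---|---|---|---|---|
| 1 month | 0.02 | 0.02 | 0.12 | 5.2% | 5.1% |
| 1 month | 0.08 | 0.08 | 0.48 | 7.6% | 7.2% |
| 2 months | 0.02 | 0.04 | 0.24 | 5.7% | 5.6% |
| 2 months | 0.05 | 0.10 | 0.60 | 9.2% | 8.5% |
| 2 months | 0.08 | 0.16 | 0.95 | 15.9% | 14.2% |

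**3. Either outcome in SD units.** This form also covers percent fat mass, for which the documents give no SD. Assumed: slope 0.01-0.05 SD per month, gap 0.5-3 months.

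- Shift = 0.01 × 0.5 = 0.005 SD, up to 0.05 × 3 = 0.15 SD.
- SE after loss = sqrt(1/85 + 1/127.5) = 0.140 SD.
- Type I error after loss: 5.0% to 18.8% over the whole range; 5.1%-6.5% at 1 month; 5.2%-11.0% at 2 months.
- Smallest difference detectable with 80% power after loss = (1.96 + 0.84) × 0.140 = 0.39 SD. The spurious shift is 0.005/0.39 = 1% to 0.15/0.39 = 38% of that.

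The shift stays near zero at half a month and matters only when a gap of about 2-3 months meets a steep slope.

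**The case against.** Four objections carry weight.

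- **Raw BMI is not established.** A reader might infer that BMI is compared untransformed. Section 2.9 says WHO tables will be used, and 2.10 also plans logistic regression, which needs a binary response. The supportable statement is that the role of the tables in the BMI outcome is undefined. This stands. It does not help percent fat mass, which those tables do not cover.
- **There is a model, and sex is in it.** A reader might infer that the plan stops at unadjusted tests and ignores sex. Section 2.10 plans a generalized linear model on the listed variables, and newborn sex is among them. The missing term is age.
- **Years apart is not ages apart.** A reader might infer that the calendar distance itself creates a bias. Both cohorts attend the same routine 2-year check, and no section shows that one attends earlier or later. This stands: the documents support a possibility that the plan neither prevents nor corrects, not a demonstrated bias.
- **This is a condensed article.** Visit windows and derived variables are often left to a fuller plan. That is fair for the window and the z-score derivation. It weighs less against the covariates, because the article itself lists them at length and ties the model to that list.

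**Conclusion.** The point holds in a limited form. The article sets out the outcomes, the covariates and the tests, and age at measurement is in none of them. With a historical control group and no window, a difference in mean visit age would pass into the contrast uncorrected. This is plain for percent fat mass and unresolved for BMI.

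The size is conditional. It rests on an assumed SD, slope and gap, none of them from the documents. For gaps of a few weeks the effect is negligible. At an assumed 2-month gap in means, type I error for BMI is 5.7%-16% with 100 v 150 children, and about 14% at worst after the 15% loss. A 2-month gap in means is large for a scheduled visit, so the upper figures mark what the plan could not correct and do not forecast the trial's error rate. The change is worth making because it costs almost nothing and protects the main objective.

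**What to change.** - Derive exact age at the 2-year measurement from birth date and visit date. The children's medical records are already a data source (2.9), so both dates should be obtainable.
- Add exact age to the list in 2.8.1 and to the generalized linear model for percent fat mass. Sex is already listed.
- State in 2.8.2 that BMI at 2 years is analysed as the WHO BMI-for-age-and-sex z-score, which gives the tables adopted in 2.9 a defined role.
- Report mean age at measurement, with its spread, by group, so that readers can see whether a gap exists.

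The cost is one derived age variable, one z-score and one model term. No new measurement or visit is needed. The adjustment removes the shift to the extent that the age effect is modelled correctly.

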### 2.9. Data Collection 

The data for the control group will be collected through a data collection sheet, specifically designed for the study, from three sources: (1)Direct questions to the parents at the one-year and two-year visits, performed by paediatricians.(2)The weight, height and BMI records of the Diraya program, both for pregnant women and children.(3)Mothers and children’s medical records from the Diraya program. The form will be subsequently computerized.

The data for the intervention group will be collected in the same way, but also at the newborn and six-month visits, developed by paediatricians.

The midwives in the usual CPPCP controls will collect the gestational and delivery variables. Nurses and paediatricians in the usual controls of the A-CAHP will collect the somatometric variables of newborns up to 2 years.

After childbirth, during the puerperal visit, the midwife will register the birth data in the Diraya program as a hospital visit. If the mother does not attend the puerperal visit, it will be the paediatricians at the newborn visit who will collect the data from birth.

The weight and height of pregnant women will be measured with an ADE (GmbH & Co, Hamburg, Germany) scale, model M304641-01, with a reading range from 2 to 250 kg and a precision of 100 g, with an ADE stadiometer coupled to the scale, model MZ10023-1, with a reading range of 60–210 cm and a precision of 0.1 cm.

Weights will be measured in the first and second year of age with the child naked on a Soehnle baby scale, reading in a range of 0–20 kg with a 10 g precision. The length will be measured with the infant in supine position with a rigid Añó-Sayol stadiometer, with a reading range of 25 to 90 cm and an accuracy of 0.5 cm. The tables of weight, length and BMI values of the WHO will be used.

The skin folds will be measured with a Holtain Skinfold Caliper plicometer with an amplitude of 0–46 mm, 0.2 mm graduation and a constant pressure of 10 g/mm^2^. They will be measured in the left side of the body, in triplicate and by a single observer for each pediatric quote, according to universally recommended techniques [62,63].

### 2.10. Data Analysis

For the statistical analysis of these data, the statistical program SPSS Version 22 software (IBM Corp, Armonk, NY, USA, 2015) will be used:

Descriptive analysis. The means and standard deviations for the quantitative variables and the absolute and relative frequencies for the qualitative ones will be determined.

Bivariate analysis. The Kolgomorov–Smirnov test will be used to determine if the quantitative variables are parametric; when the sample is less than 50, the Shapiro–Wilk test will be used. For the comparison of the dependent variables with qualitative independent ones, we will use the Student’s *t*-test and ANOVA for independent means as a test of statistical significance, and the Mann–Whitney U and the Kruskall–Wallis tests for the nonparametric ones. For independent quantitative variables, the Pearson and Spearman coefficients will be used.

Multivariate analysis. The analysis of the degree dependent variables with the independent variables will be carried out using the generalized linear model. For the linear regression, we will use the Gaussian family and as a function of the identity bond and for the binary logistic regression, the binomial family and the logit link function.

To detect differences, a significance level *p* < 0.05 will be used and the 95% confidence intervals will be calculated.

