### 2.5. Sample Size Estimation

An intentional sampling has been performed on a population of 320 births over a period of time of 1 year (2017) in the geographical situation of Puerto Real. The source of information was historical data collected from primary care management of the Bahía de Cádiz-La Janda District. It is estimated that the control group will be formed of 100 sample units and the experimental group of 150 sample units. For this configuration, assuming the randomness of the sample collected, the precision errors will be approximately 9% and 7% respectively (from the experimental group and the control group). These error levels were calculated by establishing a significance level of 95% (α = 0.05) and assuming a loss rate of 15%.

We estimate that this number of cases will guarantee the level of confidence and power necessary for statistical analysis.

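### Student's pooled-variance t-test is named for unequal groups (100 v 150); Welch's t-test would protect the 5% level and 95% interval of the control v intervention comparison if the SDs differ, at no measurable cost in power

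*Protocol article*

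**What the plan says.** Section 2.10 (Data Analysis) of the protocol article sets the tests for the two dependent variables of section 2.8.2, BMI and percent fat mass at 2 years. Against categorical variables, the parametric choice is Student's t-test and "ANOVA for independent means as a test of statistical significance". Rank tests replace them when a normality test fails. Nothing is said about variances: no check, no Welch version, no robust standard error. A Gaussian, identity-link generalized linear model follows as the multivariate analysis, with p < 0.05 and 95% confidence intervals.

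Control v intervention is not listed among the independent variables of section 2.8.1. It is, however, the comparative objective at the end of section 1, and 2.10 names no other bivariate test for it.

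Section 2.5 states that "the control group will be formed of 100 sample units and the experimental group of 150 sample units", "assuming a loss rate of 15" per cent. No SD of BMI or percent fat is given anywhere.

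**The concern.** Student's t-test estimates one common SD from both groups. When group sizes are equal, a difference in SDs does little harm. When they are unequal, the pooled standard error leans towards the SD of the larger group. If the smaller group (here control) has the larger SD, the standard error is too small, so p-values are too low and intervals too narrow. If the larger group has the larger SD, the reverse holds.

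The normality rule in 2.10 does not deal with this, because two groups can each be normal and still have different SDs. At stake are the 5% level and the 95% coverage that 2.10 promises for the main comparison. The same applies to the secondary comparisons across factor levels, where sizes may be far more unequal.

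**Working it through.** **Inputs from the document.** Groups of 100 control and 150 intervention, 15% loss (section 2.5), significance level 0.05 and 95% intervals (section 2.10). After loss: 0.85 × 100 = 85 and 0.85 × 150 = 127.5, taken as 128.

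**Assumptions.** Two-sided test and normal data unless stated otherwise. The ratio r = control SD / intervention SD is not in the document and is varied. Factor-level sizes are also assumed.

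**The plan's own figure.** Section 2.5 gives no SD, effect size or numeric power, only precision errors of about 9% and 7%. They reproduce as the 95% half-width for a proportion of 0.5 with a finite-population correction for 320 births, after loss:

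- n = 85: 1.96 × √(0.25/85) × √(235/319) = 0.1063 × 0.858 = 9.1%
- n = 127.5: 1.96 × √(0.25/127.5) × √(192.5/319) = 0.0868 × 0.777 = 6.7%

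This supports 85 and about 128 as the expected analysis sizes. (The 9% belongs to the control group and the 7% to the experimental group, the reverse of the printed labels. That is a separate matter.) These figures say nothing about a comparison of means, so they do not bear on the choice of test.

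**Size of the pooled test.** Set the intervention SD to 1.

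- True variance of the difference: T = r²/n₁ + 1/n₂
- Variance that the pooled test uses on average: P = [((n₁−1)r² + (n₂−1))/(n₁+n₂−2)] × (1/n₁ + 1/n₂)
- Pooled interval width relative to the correct width: k = √(P/T)
- True two-sided size: 2 × [1 − Φ(1.96k)]; interval coverage is one minus this.

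Example, 100 v 150, r = 1.25: T = 1.5625/100 + 1/150 = 0.02229. P = (99 × 1.5625 + 149)/248 × (1/100 + 1/150) = 1.2245 × 0.016667 = 0.02041. k = √(0.02041/0.02229) = 0.957. Size = 2 × [1 − Φ(1.875)] = 6.1%, so coverage is 93.9%.

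| r | k (100 v 150) | Student, formula (100 v 150) | Student, simulated (100 v 150) | Student, simulated (85 v 128) | Welch, simulated (both) |
|---|---|---|---|---|---|
| 0.8 | 1.045 | 4.05% | 4.0% | 4.1% | 4.9-5.0% |
| 1.0 | 1.000 | 5.0% | 4.9% | 5.1% | 4.9-5.1% |
| 1.1 | 0.981 | 5.45% | 5.5% | 5.3-5.5% | 4.9-5.1% |
| 1.25 | 0.957 | 6.1% | 6.1% | 6.0-6.1% | 4.9-5.1% |
| 1.5 | 0.926 | 7.0% | 6.9% | 6.9-7.1% | 4.9-5.0% |

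(100,000 data sets per cell in each run; ranges show repeated runs.)

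**What Welch costs in the main comparison.** At 85 v 128, equal SDs and a difference of 0.4 SD, power is 81.3% for Student and 81.2% for Welch. With gamma-distributed data of skewness 1.4 and equal SDs, Welch's size at 85 v 128 is 5.0%.

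**Secondary factor comparisons.** If a factor splits 213 children 21 v 192, with the larger SD in the small level, the pooled size is about 10% at an SD ratio of 1.25. With the ratio at 0.8 it is 1.9%. Here Welch is not free:

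- Power with equal SDs, 21 v 192, 0.6 SD difference: Student 73.9%, Welch 70.7%.
- Power with equal SDs, 11 v 202, 0.8 SD difference: Student 72.8%, Welch 65.7%.
- Welch's size with equal SDs and skewness 1.0 to 1.4: about 5.6-6.3% at 21 v 192 and 6.3-7.3% at 11 v 202. Student stays close to 5%.

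**The case against.** The strongest case against is that nothing in the document shows the SDs to differ. Sections 2.2 and 2.11 describe the quotas as socioculturally similar and the population as homogeneous. The article does not use the words equal variance, and which variance option is applied could be settled in a fuller analysis plan that is not shown. With equal SDs, Student's test is exact for normal data. All of this stands, and it is why the point cannot be called a demonstrated error. It does not remove the point: 2.10 goes into enough detail to fix tests by name, a normality rule, and a model family and link, and the tests it names pool the variance.

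A reader might infer that the hypothesis itself implies unequal spread, because an intervention that "will decrease the prevalence of childhood obesity" would shorten the upper tail in the intervention group. The document does not support this. Section 1 predicts a lower percent fat and a lower prevalence; a plain downward shift with unchanged SD gives both. If lower prevalence is modelled as a mixture (assumed obesity of 20-30% falling to 10-20%, obese children shifted by 1-2 SD), the SD ratio is only 1.02-1.10. Narrowing that arises only when the intervention works also cannot raise the false-positive rate when there is no effect; it affects interval coverage.

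One source of unequal spread does not depend on an effect. Section 2.9 assigns one skinfold observer per quota, and the control group comes from two quotas, the intervention group from four. Between-observer variation could therefore add differently to the two SDs. Its direction and size are unknown.

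**Conclusion.** The point holds as a low-cost improvement to the control v intervention comparison. At the planned sizes, Student's t-test has a true size of about 5.3-5.5% at an SD ratio of 1.1, 6.1% at 1.25 and 7% at 1.5, and about 4% if the intervention SD is larger (ratio 0.8). Interval coverage is off by the same amounts. These figures rest on normal data, a two-sided test and SD ratios that are assumed, since the document gives none. Welch's test removes the error without measurable loss.

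Two stronger readings should not be drawn. The p-values and intervals are not known to be wrong; they are unprotected against a condition that the document leaves open. And false-positive rates of twice nominal or more belong only to secondary comparisons with very unequal levels, under assumed frequencies and with the larger SD in the smaller level. There Welch has its own costs, so the case for it is not clear-cut.

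**What to change.** In section 2.10, state that the control v intervention comparison of BMI and of percent fat mass uses Welch's t-test, reported with its unequal-variance 95% interval and without a preliminary variance test. State also that the Gaussian generalized linear model uses robust (sandwich) standard errors. Without this second part the adjusted analysis would still assume constant variance.

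For comparisons across small factor levels, Welch versions are optional: they guard against a larger pooled error, but cost about 3-7 percentage points of power when SDs are equal and are slightly liberal with skewed data.

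The cost is a sentence or two in the analysis section. No extra children or data are needed, and the options should be available in the stated software.
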